# Pharmacokinetics and pharmacodynamics of azithromycin in severe malaria bacterial co-infection in African children (TABS-PKPD): a protocol for a Phase II randomised controlled trial

**DOI:** 10.12688/wellcomeopenres.16968.2

**Published:** 2023-01-10

**Keywords:** Severe Malaria, Bacterial infection, African Children, Antibiotics, azithromycin, Clinical Trial, Pharmacokinetics, Pharmacodynamics, Biomarkers

## Abstract

**Background: **African children with severe malaria are susceptible to Gram-negative bacterial co-infection, largely non-typhoidal Salmonellae, leading to a substantially higher rates of in-hospital and post-discharge mortality than those without bacteraemia. Current evidence for treating co-infection is lacking, and there is no consensus on the dosage or length of treatment required. We therefore aimed to establish the appropriate dose of oral dispersible azithromycin as an antimicrobial treatment for children with severe malaria and to investigate whether antibiotics can be targeted to those at greatest risk of bacterial co-infection using clinical criteria alone or in combination with rapid diagnostic biomarker tests.

**Methods: **A Phase I/II open-label trial comparing three doses of azithromycin: 10, 15 and 20 mg/kg spanning the lowest to highest mg/kg doses previously demonstrated to be equally effective as parenteral treatment for other salmonellae infection. Children with the highest risk of bacterial infection will receive five days of azithromycin and followed for 90 days. We will generate relevant pharmacokinetic data by sparse sampling during dosing intervals. We will use population pharmacokinetic modelling to determine the optimal azithromycin dose in severe malaria and investigate azithromycin exposure to change in C-reactive protein, a putative marker of sepsis at 72 hours, and microbiological cure (seven-day), alone and as a composite with seven-day survival. We will also evaluate whether a combination of clinical, point-of-care diagnostic tests, and/or biomarkers can accurately identify the sub-group of severe malaria with culture-proven bacteraemia by comparison with a control cohort of children hospitalized with severe malaria at low risk of bacterial co-infection.

**Discussion**: We plan to study azithromycin because of its favourable microbiological spectrum, its inherent antimalarial and immunomodulatory properties and dosing and safety profile. This study will generate new data to inform the design and sample size for definitive Phase III trial evaluation.

**Registration: **
ISRCTN49726849 (27
^th^ October 2017).

## Abbreviations

AQUAMAT: Artesunate versus Quinine in the treatment of severe falciparum Malaria in African children AUC24h: area under the curve at 24 hours; AVPU: alert, voice, pain, unresponsive: system of recording patient’s level of consciousness; CRF: case report form; CRP: C-reactive protein;
*E. coli*:
*Escherichia coli*; ETAT: emergency triage assessment and treatment; FEAST: Fluid Expansion As a Supportive Therapy; GCP: Good Clinical Practice Hb: haemoglobin; IBI: invasive bacterial infection; ICREC: Imperial College Research Ethics Committee; KWTRP: KEMRI Wellcome Trust Research Programme; MIC: minimum inhibitory concentration MRRH: Mbale Regional Referral Hospital; MRRH-REC: Mbale Regional Referral Hospital Research Ethics Committee; MRC: Medical Research Council; NTS: non-typhoidal salmonella; PCT: procalcitonin; PD: pharmacodynamic;
*P. falciparum* HRP2:
*Plasmodium falciparum* histidine-rich protein 2; PK: pharmacokinetic; PKPD: pharmacokinetic-pharmacodynamic; RDT: rapid diagnostic test; TRACT: TRansfusion and Treatment strategies of severe Anaemia in African children Trial; WHO: World Health Organization.

## Introduction

*Plasmodium faliciparum* malaria remains to be a common cause of hospital admission in much of sub-Saharan Africa, and plays a substantial role in under five-year mortality
^
1
^. Strategies to control or prevent malaria (including vaccines) have so far offered limited short-term protection. Over the past decade some African countries have either documented no decline
^
2
^, an increase in hospitalisations with severe
*P. falciparum* malaria
^
3
^ or a resurgence of severe malaria following a period of sustained control. Thus, prevention strategies alone in many parts of Africa will not adequately address the burden that malaria poses on health services, particularly in countries where transmission is high. Even with the best (evidence-based) antimalarial treatment artesunate, children in the Artesunate versus Quinine in the treatment of severe falciparum malaria in African children (AQUAMAT) trial had an overall mortality of 6–8.5%
^
4
^. The trial population were selected pragmatically (defined by parasite-positivity and the admitting clinician’s desire to use parenteral rather than oral antimalarials) for generalisability of the results. However, mortality in children with severe malaria would almost certainly be substantially higher outside a Good Clinical Practice (GCP)-run trial and outside selected centres with a strong track record of research; and with more stringent clinical criteria defining severe malaria
^
5
^. Thus, there is substantial potential for clinical trials addressing the safety and efficacy of adjuvant supportive therapies to not only close existing gaps in the severe malaria treatment algorithm, but also substantially improve outcomes
^
6
^.

Children with severe malaria and bacterial co-infection, largely due to enteric Gram-negative organisms with a predominance of non-typhoidal salmonella (NTS) species, have substantially higher rates of in-hospital and post-discharge mortality
^
7
^. An estimated one third of all severe malaria deaths in African children are attributable to bacterial co-infection
^
8
^. Current guidance and evidence for treating co-infection in children is lacking, and there is no consensus on the dosage or length of treatment required. Identifying which children genuinely have bacterial co-infection is practically impossible. The indiscriminate use of antibiotics is both financially costly and may perpetuate the rise of antibiotic resistance. Establishing which children with malaria are at greatest risk of bacteraemia is critical to pragmatically inform a policy for targeted antibiotic therapy that could substantially reduce malaria-associated mortality while minimising the risks of excess antibiotic prescribing.

### Bacterial co-Infection in severe malaria

We conducted a systematic review in 2013 examining studies among children with malaria admitted to hospitals or outpatient clinics in sub-Saharan Africa reporting invasive bacterial infection (IBI)
^
9
^. We identified a total of 25 studies across 11 African countries which fulfilled the inclusion criteria. These comprised of 20 cohort analyses, two randomised controlled trials and three prospective epidemiological studies. We initially compared the prevalence of IBI in 20,889 children who were hospitalised with all-severity malaria to 27,641 children hospitalised with a non-malarial febrile illness. The mean prevalence of IBI was 5.58 (95% CI 5.5 to 5.66%) in children with malaria and 7.77% (95% CI 7.72 to 7.83%) in non-malaria illness. In the meta-analysis involving 10 studies (n=7,208) of children with severe malaria the mean prevalence of IBI was 6.4% (95% confidence interval (CI) 5.81 to 6.98%). Ten of the 25 studies reported mortality stratified by bacterial infection status. Case fatality was higher at 81 of 336, 24.1% (95% CI 18.9 to 29.4) in children with malaria/IBI co-infection compared to 585 of 5,760, 10.2% (95% CI 9.3 to 10.98) with malaria alone. In seven of 14 hospital studies, NTS was the commonest isolate and one other study listed enteric Gram-negative organisms as the most common isolates in malaria-infected children
^
9
^. Thus, enteric Gram-negative organisms, and NTS in particular, cause the vast majority of bacteraemia co-infections
^
9
^. Moreover, the poor sensitivity of blood cultures (due to low blood volumes in children and previous antibiotic use) means that the true prevalence of bacteraemia co-infection is likely to be significantly higher and ‘nosocomial bacteraemia’ will be acquired in a further 2–3.5% of children receiving a transfusion (commonly prescribed in severe malaria) due to poor quality.

### Current management recommendations

Current recommendations indicate that antibiotics should be given to ‘all children with suspected severe malaria in areas of moderate and high transmission until a bacterial infection is excluded… and should be based on culture and sensitivity results or, if not available, local antibiotic sensitivity patterns’
^
10
^. However, many hospitals in Africa lack culture facilities or access to such data; thus, best practice is not obvious. In one study almost 50% of bacterial isolates were resistant to the antibiotics most commonly recommended (chloramphenicol and gentamicin for empirical use)
^
11
^. In the specific case of NTS, the efficacy of gentamicin is doubtful and susceptibility testing unreliable due to this infection’s intracellular nature. For newer and broad-spectrum antimicrobials, apart from financial considerations, there are concerns that over-use could lead to resistance. A systematic review of studies and trials of supportive therapy in severe malaria was undertaken. Whilst definitive evidence for parenteral antimalarial treatment has now been provided
^
4,
10
^, progress on supportive therapeutics has been limited. To date, of the 34 clinical trials involving adjunctive therapies in severe malaria, including 20 (59%) in African children, none of these trials have targeted bacterial co-infection
^
6
^. Searching ClinicalTrials.gov and ISRCTN we found no trials addressing anti-microbial treatment of bacterial co-infection in severe malaria.

### Justification for azithromycin for malarial sepsis

There are several reasons why we consider that azithromycin represents an attractive option in such an approach. Given the worldwide threat of antimicrobial resistance, the underlying principle is to test the narrowest spectrum antibiotic that would be practical, generalisable and plausibly have reasonable efficacy. There are several reasons for selecting azithromycin as the targeted antimicrobial invention. Primarily, it is active against NTS, the commonest cause of bacterial co-infection in severe malaria
^
9
^, against which currently recommended antimicrobials are ineffective (e.g. chloramphenicol, ampicillin/gentamicin combination)
^
11
^. It is also active against a range of other gram-negative and gram-positive organisms, although it is less active against
*Escherichia coli* and Klebsiella spp. The alternative (effective) antimicrobial therapies we considered, given that they would likely be active against NTS
^
12
^, were, first, a full course (~seven days) of parenteral third generation cephalosporins. This has feasibility concerns as it would prolong hospital stay (median four-five days), and would be difficult (and potentially unethical) to blind. In contrast to macrolides, which are not widely used in other childhood diseases
^
13
^, adding a major new indication for third-generation cephalosporins (severe malaria) also risks widening their use even further, and thus increasing the threat of antimicrobial resistance to a second-line antibiotic recommended for other common childhood diseases. Quinolones (e.g. ciprofloxacin) are another alternative strategy, given their superior antimicrobial activity against Salmonella species
^
13
^,
*E. coli* and Klebsiella spp. However, resistance is generated through single mutations in the housekeeping genes gyrA or gyrB; and can be detected shortly after administration in healthy volunteer studies, suggesting resistant variants are commonly present at low levels or easily acquired
^
14
^. A recent study found pathogenic ciprofloxacin-resistant
*E. coli* were highly prevalent in healthy children and their mothers
^
15
^, raising the possibility that widespread use in children with severe malaria without evidence of bacterial infection could have serious unintended consequences. Moreover, in most countries the use of fluoroquinolones in children is relatively contraindicated (due to concerns over musculoskeletal side-effects) except for use in multi-drug resistant infections where there are no suitable alternatives
^
13
^. Finally, although cephalosporin and quinolone resistance rates are currently relatively low in relevant organisms in some African countries
^
12
^, they are much higher in Asia
^
13
^, limiting generalisability of the trial’s findings worldwide.

Other favourable properties of azithromycin include:

1.   It is licenced for use and has a good safety profile in children.

2.   Azithromycin’s pharmacokinetic (PK) properties include extensive tissue distribution, prolonged phagocyte concentrations, and a longer elimination half-life (~50hours) than other macrolides, thus enabling once-daily dosing (versus more frequent dosing required for clindamycin)
^
16
^.

3.   Its long half-life is also likely to protect children at increased risk of NTS bacteraemia following a malaria episode
^
17
^.

4.   An accumulating body of evidence indicates some macrolides have beneficial properties independent of their antimicrobial effects
^
18
^. It is thus plausible that azithromycin may also have a beneficial effect on immune activation and gut inflammation.

5.   A further consideration is that azithromycin is a weak antimalarial
^
19
^, and has proved effective in treating
*P. falciparum* malaria in early phase trials when used in combination with faster-acting antimalarials.

6.   Dispersible azithromycin is currently widely available at an affordable price, costing 0.40 euros per 100mg dose in an oral formulation. i.e. two-six Euros per five-day paediatric treatment course.

### Target population

Current recommendations indicate that antibiotics should be given to ‘all children with suspected severe malaria in areas of moderate and high transmission until a bacterial infection is excluded’
^
10
^. However, WHO definitions of severe malaria are very broad, incorporating high parasitaemia as a single criterion, and are thus applicable to a large proportion of paediatric admissions in such regions, with a relatively overall low case fatality (1–2%)
^
20
^, who are unlikely to benefit from antimicrobial therapy as a group. For this study (and in a future trial) we aim to target antibiotics to children with the highest risk of bacterial co-infection, meeting ‘Teule’ criteria
^
11
^: that is, with malaria (positive blood film or ParacheckTM rapid diagnostic test, RDT); temperature > 38°C or < 36°C; and ≥1 of prostration, respiratory distress, haemoglobin (Hb) <5g/dl or HIV. These criteria identified 85% of bacterial co-infections, with a three-fold higher mortality than children admitted with malaria without these criteria.

### Credibility: can antibiotics be targeted?

A major legitimate concern is whether future management guidelines can be implemented which try to reduce the overuse of antibiotics where microbiology services are poor or non-existent, thus an approach to targeting only those with IBI is not feasible in much of Africa. Within the context of this study and to inform a future trial, we aim to investigate approaches (that may be generalizable in future) to targeting antibiotics. We propose to use (i) simple clinical criteria: proposed by Nadjm
*et al.*
^
11
^, the Teule criteria identifies 85% of malaria cases with culture-proven bacteraemia: a pathogen was isolated from 20% children meeting these criteria. Simple and objective criteria identifying those at risk would be more generalizable outside research centres and would be validated in this study. (ii) Potential biomarkers: even when quality-controlled blood-culture facilities are available, low sensitivity (due to frequent pre-hospital antibiotic therapy, low culture volumes from children and low bacterial density) and long times to culture-positivity (typically two-three days) mean that alternative approaches for identifying concurrent gram-negative bacteraemia would be highly valuable.

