### Our hypotheses

1. Azithromycin given to children once-daily for five days in addition to standard treatment of severe malaria (including anti-malarials) can provide adequate dosing in children admitted to hospital with severe malaria.

2. Children with severe malaria and culture-proven bacteraemia can be accurately identified using clinical criteria alone or in combination with a rapid diagnostic biomarker tests, in comparison with a control cohort of children hospitalized with severe malaria but not meeting Teule criteria, at low risk of bacterial co-infection.

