### Inclusion criteria

*Cases:*

105 children aged six months to 12 years at admission to hospital with
*P. falciparum* malaria (on either blood film or ParacheckTM RDT) and all of the following:

i) Axillary temperature >38°C or <36°C.

ii) Teule severity criteria
^
11
^: any one of the following: prostration; respiratory distress; severe anaemia (haemoglobin<5g/dL) or HIV infection.

iii) Parents willing/able to provide consent.

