### Controls

The control cohort of children (n=50) are those hospitalised with severe malaria but not meeting Teule criteria (i.e., low risk of bacterial co-infection) whose parents are willing/able to provide consent.

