## Sampling

### Sample size determination

A formal sample size was not calculated. Phase I/II trials are an important step in the assessment of new or existing interventions providing the first data on the feasibility of using a product in a new application. They assess the effect of products (how well they work), and the side effects they may have. They are not usually designed to compare superiority of different products or interventions.

The aim is to generate pilot efficacy data on the optimal azithromycin dose for children with severe malaria, which will inform the design of a later larger Phase III trial. The numbers required to address the trial objectives are therefore balanced against the exposure of children in these settings to a therapeutic intervention (dose) for which there are limited data to date.

The overall sample size for the trial will be 105 children randomised 1:1:1 to receive 10, 15 or 20mg/kg azithromycin (based on weight-bands). This is sufficient for the PKPD sampling and modelling to determine an optimal dose in children with severe malaria using change in CRP at 72 hours, and microbiological cure (seven-day) alone and with seven-day survival. This is under the assumption that 20% of enrolled children (meeting Teule severity criteria) will have bacteraemia and that 80% of these infections will be caused by NTS or other enteric gram-negative organisms based on previous research. 

Based on Monte Carlo simulations, we expect that all dose groups should reach the population reference target (adult) AUC24h of at least 3.4 h*mg/L
^
24
^, although there are no data on absorption in severe malaria, which is characterised by impaired gut function
^
25
^, hence the need for this pilot. Along with the 105 children with Teule criteria we will enrol 50 children meeting other inclusion criteria but without Teule criteria (and without any exclusion criteria) into the control group.

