### Study methods and procedures

Eligible children will be identified by the nurse and clinician on duty and registered in the eligibility screening log. A member of the trial team will then perform a rapid structured assessment of heart rate, oxygen saturation (pulse oximetry), respiratory rate, axillary temperature, blood pressure, markers of shock (capillary refill time, pulse volume and assessment of lower limb temperature) and severity (conscious level and respiratory distress). Children who are potentially eligible with suspected severe malaria will have a rapid bedside malaria test (detecting
*P. falciparum* histidine-rich protein 2, HRP2) to determine malaria status and eligibility.

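### Enrolling by Teule status at a fixed 105:50 quota lets the study check the predictive values of the Teule criteria, but not, from the enrolled children alone, their sensitivity or specificity

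*Protocol article*

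**What the plan says.** The section on whether antibiotics can be targeted gives two figures for the criteria: "the Teule criteria identifies 85% of malaria cases with culture-proven bacteraemia: a pathogen was isolated from 20% children meeting these criteria". The first is a sensitivity and the second a positive predictive value. The same section promises that "Simple and objective criteria identifying those at risk would be more generalizable outside research centres and would be validated in this study".

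The second hypothesis makes this an aim of the study: "Children with severe malaria and culture-proven bacteraemia can be accurately identified using clinical criteria alone", or in combination with a rapid biomarker test, in comparison with a control cohort. The general and specific objectives repeat it.

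Enrolment is by Teule status. The inclusion criteria for cases specify "105 children aged six months to 12 years at admission to hospital with" malaria, abnormal temperature and at least one Teule severity sign. Of the other group the article says "The control cohort of children (n=50) are those hospitalised with severe malaria but not meeting Teule criteria". The sample size section confirms the quota: "Along with the 105 children with Teule criteria we will enrol 50 children meeting other inclusion criteria but without Teule criteria". It also assumes a yield: "This is under the assumption that 20% of enrolled children (meeting Teule severity criteria) will have bacteraemia".

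Table 3 schedules an admission blood culture without restricting it to cases, so bacteraemia status should be known in both groups. Screened children are "registered in the eligibility screening log". No section links that log to the accuracy analysis, and none states sampling fractions or how the 50 controls are chosen from the Teule-negative admissions.

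**The concern.** When children are selected on the test result, the number of test-positives and test-negatives is set by design. The bacteraemia rate within each group is then estimable. Sensitivity and specificity also need the ratio of positives to negatives among all severe-malaria admissions, and the quota replaces that ratio. No analysis confined to the 155 children can restore it, so this is a property of the enrolment plan and not a detail left to an analysis plan. Any rule that combines Teule status with a biomarker, if evaluated on the pooled children, inherits the problem.

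Targeting is one of the two principal objectives. The Discussion says that the risk strata of a future Phase III trial could use the Teule criteria and would be informed by this pilot. One of those strata compares standard of care with no antibiotics in low-risk children. A sensitivity inflated by the quota would make the criteria appear to miss fewer bacteraemic children than they do.

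**Working it through.** **Inputs.** 105 Teule-positive and 50 Teule-negative children (inclusion criteria, controls). Sensitivity 85% and positive predictive value (PPV) 20% (section on targeting; the 20% again under sample size). Prevalence of invasive bacterial infection in severe malaria 6.4%, 95% CI 5.81 to 6.98% (section on bacterial co-infection). The 85% comes from a cited study whose counts are not given, so it cannot be reproduced here. The expected yield can: 105 × 0.20 = 21 bacteraemic cases and 84 non-bacteraemic cases.

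**Step 1: implied source population.**
- Teule-positive share = sensitivity × prevalence / PPV = 0.85 × 0.064 / 0.20 = 0.272.
- Bacteraemia rate in Teule-negatives = 0.15 × 0.064 / (1 − 0.272) = 0.0132.
- Implied specificity = 0.728 × (1 − 0.0132) / (1 − 0.064) = 0.768.

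**Step 2: enrolled sample.**
- Teule-positive share = 105/155 = 0.677, not 0.272.
- Bacteraemic controls expected = 50 × 0.0132 = 0.66, leaving 49.34 non-bacteraemic.
- Pooled sensitivity = 21 / (21 + 0.66) = 0.970, against 0.85.
- Pooled specificity = 49.34 / (49.34 + 84) = 0.370, against 0.768.
- Chance of no bacteraemic control = (1 − 0.0132)^50, about 0.51. Pooled sensitivity would then be exactly 100%.
- With 21 of 105 cases positive, pooled specificity cannot exceed 50 / (50 + 84) = 0.373, whatever the population value.

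**Step 3: dependence on prevalence.** The article says that the true prevalence is probably higher than cultures show but gives no figure. The values of 10% and above are therefore assumptions.

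| Prevalence | Implied Teule-positive share | Sensitivity, pooled vs source | Specificity, pooled vs source |
|---|---|---|---|
| 5.81% | 24.7% | 97.3% vs 85% | 37.0% vs 79.0% |
| 6.4% | 27.2% | 97.0% vs 85% | 37.0% vs 76.8% |
| 6.98% | 29.7% | 96.6% vs 85% | 37.0% vs 74.5% |
| 10% | 42.5% | 94.2% vs 85% | 36.7% vs 62.2% |
| 15.9% | 67.7% | 85.0% vs 85% | 35.5% vs 35.5% |
| 18% | 76.5% | 78.5% vs 85% | 34.5% vs 25.4% |

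The break-even prevalence is 0.677 × 0.20 / 0.85 = 0.159, where the source share equals the quota.

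**Step 4: what the sample does estimate.** With 21 of 105 cases positive, the PPV is 20%, exact 95% interval 12.8% to 28.9%. With 0 of 50 controls positive, the upper exact limit for bacteraemia in Teule-negatives is 7.1%.

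**Step 5: what weighting could add.** If the Teule-positive share q were known, weighted sensitivity = q·p₁ / (q·p₁ + (1 − q)·p₀), where p₁ and p₀ are the observed rates in cases and controls. At q = 0.272, p₁ = 0.20 and 0 of 50 controls positive, the point estimate is 100%. The control upper limit gives 0.0544 / (0.0544 + 0.728 × 0.0711) = 51%. Simulation under the Step 1 inputs gives a 2.5th to 97.5th percentile range of 57% to 100%.

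**The case against.** The strongest reply is that the article never says it will compute Teule sensitivity or specificity on 155 pooled, unweighted children. The biomarker sub-study names cases and controls separately, the statistical analysis section gives no diagnostic-accuracy method, and an analysis plan may exist that handles this. That stands: the percentages above show what a pooled calculation would give, not what the trial plans to report. It does not remove the point, because no method applied to the enrolled children alone supplies the missing share.

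Second, the word validated need not mean sensitivity. The 20% yield can be checked in the 105 cases and the negative predictive value in the controls, so validation is not lost altogether. That also stands, and it is why the claim should be narrowed rather than deleted.

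Third, the illustration mixes sources. The 85% and 20% are stated for malaria cases, the 6.4% for severe malaria, so 27.2% is a derived share and not an observed one. Both the size and the direction of the bias depend on it. This is correct and limits the conclusion.

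Fourth, Teule accuracy is not a listed primary or secondary outcome, and this is a pilot without a formal sample size. That limits the severity, but targeting is still a principal objective.

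**Conclusion.** The point holds in limited form. The enrolled children alone support the predictive values of the Teule criteria and do not identify their sensitivity or specificity. This follows from the quota and needs no assumption about prevalence. The size does: 97% against 85% and 37% against 77% rest on combining 85%, 20% and 6.4% across populations.

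A reader might infer more, in three ways that the documents do not support:
- That sensitivity and specificity can never be recovered. Weighting by known sampling fractions could recover them in principle, though sensitivity would be very imprecise.
- That the quota must inflate sensitivity. Above about 15.9% prevalence it would deflate it.
- That the point is unaffected by how controls are defined. Selection on Teule status is common to all the descriptions, but the illustration and the weighting are not robust to them. The controls section specifies severe malaria without Teule criteria. The sample size section adds the other inclusion criteria, which may include the temperature criterion. The treatment allocation section describes the comparator cohort as having non-severe malaria. If controls are not the true complement of the cases, weighting fails.

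The dose objective is unaffected.

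**What to change.** 1. Limit the validation sentence in the section on targeting to predictive values, and read the second hypothesis and the matching objectives in that sense.
2. Report bacteraemia prevalence in Teule-positive and Teule-negative children separately, each with an exact 95% interval.
3. Do not report unweighted pooled sensitivity or specificity, either for Teule status or for Teule-plus-biomarker rules.
4. Reconcile the three control descriptions and state which admissions the controls represent.
5. Give weighted sensitivity and specificity only if the screening log holds Teule status for all severe-malaria admissions and the controls are a representative sample of the Teule-negative ones. State that the sensitivity interval will be very wide: under the illustrative inputs about 0.66 bacteraemic controls are expected, with about a 51% chance of none.

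Making biomarker accuracy within the 105 cases the main biomarker analysis is optional.

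The cost of items 1 to 4 is wording and reporting, which is still possible because the article says that recruitment is complete and analysis is under way. Item 5 costs a tally if the log is complete. The article does not show that it is, and with recruitment closed, missing entries can no longer be logged prospectively. What is given up is a direct check of the 85% figure.
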